### Secondary outcome measure: prevalence of HAI

The prevalence rate is operationalized as the number of HAI per 100 patients. This will be assessed with the PREZIES module of the national surveillance system of HAI during the 18 month intervention period (http://www.prezies.nl/). This module is comparable to CDC surveillance methods (http://www.cdc.gov/HAI/surveillance/monitorHAI.html). Point-prevalence will be measured at T1, T2, T3 and T4 in all experimental and control units, in a given time slot (two week period). All prevalence data will be collected by a qualified ICP, who will be trained before commencement of the study. At each data collection point two point-prevalence measurements will collected, and the data of the two measurements averaged to adjust for fluctuations.

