## Methods/Design

### Study design

The ACCOMPLISH package will be tested in a two-arm cluster randomized trial in 16 hospitals in the Netherlands (eight intervention and eight control) in one intensive care unit (ICU) and one surgical ward per hospital. In eight hospitals *ACCOMPLISH *will be introduced, while eight control hospitals will maintain normal HH practices. All infection prevention activities as well as any large outbreaks or other major events which might influence HH behaviour will be documented in a process evaluation. The primary outcome measure will be the observed hand hygiene compliance rate, measured at baseline (T1) and after 6 (T2), 12 (T3) and 18 (T4) months. As a secondary outcome measure the prevalence of HAI will be measured at the same time points. At each time point data identifying process indicators will be collected. The process evaluation will also include determinants of implementation, namely the social-political context, the organization, the adopting person (i.e. the HCW), the innovation itself and the facilities needed for implementation [13]. See figure 1 for an overview of the data collection activities.

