### Sample size calculations

Compliance: Compliance rates are expected to increase from 20% at baseline to 50% twelve months after the intervention. Assuming 120 observed opportunities for compliance per ward per measurement moment and a 10% heterogeneity between wards, a power of 93% was calculated with two-sided alpha = 0.05 for this design. In each hospital one ICU and one surgical ward will be included in the study.

Prevalence of HAI: 8568 patients are expected to be included in this study. Based on PREZIES data a baseline prevalence of HAI of 12% in the surgical ward and of 25% in the ICU is estimated [28]. Approximately 30% of these infections are exogenous and based on international literature a reduction of 40% of the exogenous part of these HAI can be expected in the intervention hospitals [29]. This will lead to a reduction in HAI in the surgical ward from 12-> 10%, and in the ICU from 25->22%. Based on an average reduction of 16-> 14% (when pooling the data) a power of 73% with a two-sided alpha = 0.05 was calculated. Since baseline measurements will be collected in all units this will enable comparison within units, substantially increasing the power.

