### Data analysis

Process indicator questionnaires: These will be analysed with multivariable linear regression analysis, with self-reported compliance (never-always on a 10-point scale) as primary outcome variable. The determinants included in the questionnaire will include the socio-political context, the organization, the adopting person or HCW, the innovation and the facilities needed to implement the innovation [13]. Furthermore behavioural determinants will be included in the questionnaire, including attitudes, social norms, perceived behavioural control, intention, habit, knowledge of the guidelines and patient safety culture (as measured by the ComPaz questionnaire) [30].

Randomised controlled trial: The effect of the intervention strategy on the overall compliance rate among HCW (logistic regression analysis), and on prevalence of HAI will be assessed. Multilevel analysis will be performed to compensate for the clustered nature of the data (HCW are clustered within wards), using mixed linear modelling techniques.

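### The 73% power for HAI treats 8568 patients as independent, but each unit is surveyed twice per time point with no allowance for patients present at both surveys

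*Protocol article*

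**What the plan says.** The section on the secondary outcome defines it thus: "The prevalence rate is operationalized as the number of HAI per 100 patients". Point prevalence is measured at T1 (baseline), T2, T3 and T4 in every unit, in a time slot described as a two-week period. It then adds: "At each data collection point two point-prevalence measurements will collected, and the data of the two measurements averaged to adjust for fluctuations". The section says nothing about how far apart the two surveys are or what happens to a patient present at both.

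Under Sample size calculations, the article states that "8568 patients are expected to be included in this study" and that "a baseline prevalence of HAI of 12% in the surgical ward and of 25% in the ICU is estimated". It pools the two ward types to a fall from 16% to 14%, for which "a power of 73% with a two-sided alpha = 0.05 was calculated". It adds, without a figure, that within-unit comparison with baseline will increase the power substantially. The Study design section gives "16 hospitals in the Netherlands (eight intervention and eight control) in one intensive care unit (ICU) and one surgical ward per hospital".

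Under Data analysis, "Multilevel analysis will be performed to compensate for the clustered nature of the data", with the clustering described as healthcare workers within wards. Repeated patients are not mentioned.

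**The concern.** A point-prevalence survey records whoever is in the unit that day. Two surveys of the same ICU and surgical ward within about two weeks will share some patients. Those with an HAI are the more likely to be seen twice, since the Background itself links HAI to longer stays. The second record of such a patient adds little new information.

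If 8568 is the total over both surveys, the number of independent patients behind the 73% is too high. The starting power is already below 80%. HAI is secondary, so the compliance conclusion is untouched. However, the difference in HAI prevalence is also the denominator of the incremental cost-effectiveness ratio in the Economic Evaluation, so its precision matters there too.

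**Working it through.** **Inputs from the protocol article.** Total 8568; 16% against 14%; two-sided alpha 0.05; stated power 73%; 8 against 8 hospitals with two units each (32 units); four time points; two surveys per time point; baseline prevalence 12% (surgical) and 25% (ICU).

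**Inputs not in the article (assumptions).** Share *o* of patients common to both surveys; within-patient correlation *r* of HAI status; ICC.

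**1. Reproduce the stated power.** With n = 8568/2 = 4284 per arm:

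- SE = √[(0.16×0.84 + 0.14×0.86)/4284] = 0.00771
- z = 0.02/0.00771 = 2.593, and 2.593 − 1.960 = 0.633
- power = Φ(0.633) = 73.7% (73.6% with pooled variance under the null)

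The stated 73% is therefore a calculation on 8568 independent patients with a design effect of 1.

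**2. Does 8568 sum both surveys?** The article does not say. Its figures can be checked for plausibility:

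- Pooling 12% and 25% to 16% needs an ICU share of (16 − 12)/(25 − 12) = 4/13, about 31%.
- 8568/(16 hospitals × 4 time points) = 133.9 patients per hospital per time point.
- As one census, that is about 41 ICU and 93 surgical patients, in one ICU and one surgical ward.
- Split over two surveys, it is about 21 and 46.

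The second reading is easier to credit as an average for a sample that includes small general hospitals. This is an inference from the numbers.

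**3. Effect of repeat patients, if 8568 sums both surveys.** For two surveys of equal size, the variance of their average is inflated by 1 + *o*×*r*, so effective n per arm = 4284/(1 + *o*×*r*).

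| Overlap *o* | Correlation *r* | Factor | Effective total | Power |
|---|---|---|---|---|
| 5% | 0.5 to 1 | 1.025 to 1.05 | 8359 to 8160 | 72.6% to 71.6% |
| 10% | 0.5 to 1 | 1.05 to 1.10 | 8160 to 7789 | 71.6% to 69.6% |
| 20% | 0.8 | 1.16 | 7386 | 67.3% |
| 50% | 0.8 | 1.40 | 6120 | 59.2% |

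An overlap of 24% to 50% would follow from exponential stays with a mean of 7 to 10 days and surveys 7 to 10 days apart (e^(−10/7) = 0.24; e^(−7/10) = 0.50). These stays and spacings are also assumed.

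**4. Other reasons why the independent number is too high.** Each is taken alone, starting from 73.7%:

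- *Baseline patients.* If 8568 covers T1 to T4 in equal parts, T2 to T4 contribute 6426, or 3213 per arm, and power is 61%.
- *Clustering.* 8568/32 = 267.75 patients per unit. With the design effect 1 + 266.75×ICC, an assumed ICC of 0.001 gives 1.27 and 63% power; 0.005 gives 2.33 and 40%; 0.01 gives 3.67 and 27%.

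**5. Cost of averaging itself.** With no overlap, an equally weighted mean of surveys of sizes a and b has variance 0.25×(1/a + 1/b)×(a + b) relative to pooling. For 30 and 36 patients this is 1.008; for 10 and 14 it is 1.029.

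**The case against.** The article says only that 8568 patients are expected. If these are distinct patients, overlap does not reduce the 73%, and all that is left is a wording question. That stands: step 2 makes the other reading more likely but does not prove it.

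The size of the loss rests on overlap and correlation values that the article does not give, and at small overlap it is only 1 to 4 points. That also stands. The missing design effect and the baseline patients may well matter more, and the unquantified gain from within-unit comparison could offset part of the loss. If T1 patients are already in the 8568, however, that gain would partly use them twice.

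A reader might infer that averaging the two surveys contradicts a patient-level power calculation. It does not: with similar census and no overlap, the average carries the same information as the pooled data. Nor does the article say that patient records are discarded or that the mean is unweighted. A marked precision loss from averaging needs a census that changes sharply between surveys, and nothing in the article indicates that; step 5 shows 1% to 3% for modest differences. Averaging to one value per unit and time point is also a legitimate cluster summary that avoids treating a repeated patient as two independent observations in the analysis.

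Finally, the handling of repeat patients could be left to a fuller document. The power figure, however, is stated here, and it reproduces only under independence.

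**Conclusion.** The point holds in a limited form. The 73% is reproduced (73.7%) only with 8568 independent patients, while the design surveys the same units twice per time point, apparently within one two-week slot, and states no allowance for patients seen at both. If 8568 sums both surveys, true power is below the stated figure for any overlap with positive correlation: about 70-73% at 5-10% overlap, and 67% to 59% at 20-50% overlap with correlation 0.8. If 8568 counts distinct patients, this particular loss disappears.

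That patients are in fact counted twice is something a reader might infer, but the article does not state it. Nor is overlap necessarily the main weakness of the figure. Clustering (about 40% power at an assumed ICC of 0.005) and restriction to T2-T4 (about 61%, if T1 is in the total) act in the same direction. A restated power should deal with all three together.

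**What to change.** 1. State whether 8568 counts distinct patients or patient-survey records, whether it includes T1, and how far apart the two surveys are.
2. Keep the records of both surveys with a pseudonymous patient code. Analyse them together in the planned multilevel model, with hospital and unit as levels and repeated patients accounted for. If averaging is kept, weight the two surveys by their census.
3. Restate the power on post-baseline data, with a stated ICC and an allowance for repeat patients, and put a figure on any gain claimed from the baseline comparison.

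The definition of the outcome as HAI per 100 patients need not change on this ground. The cost is one code on the survey form, some analysis wording and a less favourable stated power. No extra surveys or patients are needed.

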## Process indicators

In order to identify barriers and facilitators of the implementation of ACCOMPLISH, information on process indicators will be collected at T1, T2, T3 and T4. Special attention will be paid to the different types of determinants of innovation in healthcare, which can be divided into 5 groups, namely the socio-political context, the organization, the adopting person or HCW, the innovation and the facilities needed to implement the innovation [13]. Information will be collected on HCW experiences with components of the intervention, on self-reported compliance rates and behavioural and environmental determinants of non-compliance using a questionnaire based on the Theory of Planned Behaviour in addition to constructs identified in qualitative research [10,25]. It will provide information about dissemination requirements, needed for large scale application. Other process indicators identifying possible infection prevention activities outside the intervention package will be collected during the entire intervention.

## Economic Evaluation

An ex-post economic evaluation of the ACCOMPLISH package to improve compliance to hand hygiene guidelines compared to a control group, from a healthcare perspective will be performed in accordance with the Dutch guidelines [26].

A cost-effectiveness analysis will assess the balance between costs of the intervention and effects of improved HH, from a healthcare perspective. Costs for all separate actions and time used by all individual healthcare professionals, the training program, costs for the electronic alcohol based hand rub dispensers and all other materials will be measured from a healthcare perspective for the intervention package. Table 2 gives an overview of the costs which will be calculated.

**Table 2 T2:** Costs to be calculated for cost-effectiveness analysis

Intervention component	Costs to be calculated
Alcohol dispensers	1. costs of alcohol rub dispenser (purchase + maintenance)
	2. costs of placement (staffing costs)
	3. costs of more frequent refilling due to increased use of alcohol hand rub (compared to control unit)
	4. costs of alcohol hand rub due to increased use (compared to control unit)
	5. extra staffing time needed to perform HH compared to control unit (# times HH is performed extra X average time needed for HH as measured by new dispenser)

Feedback component	1. promotional materials for feedback element (posters, newsletters)
	2. costs for rewards
	3. extra time needed to incorporate feedback into daily work activities (i.e. during existing staff meetings)

Training component	1. production costs social and web based training
	2. maintenance costs web based training
	3. staffing costs for staff time needed to participate in training sessions

Overall	1. staffing costs continuous maintenance intervention components by infection control nurse
	2. training infection control nurse prior to intervention

For the calculation of the saving due to reduced healthcare use of patients without HAI total intramural medical costs of comparable patients with HAI will be calculated.

For the most important cost items, unit prices will be determined by following the micro-costing method [27], which is based on a detailed inventory and measurement of all resources used. Resource costs arise within the hospital and consist of outpatient visits, inpatient days, use of the operation room, radiology examinations, blood tests, etc. Real medical costs will be calculated by multiplying the volumes of healthcare use with the corresponding unit prices. For instance, the calculation of the costs of complications and prolonged hospital stay will consist of detailed measurement of investments in manpower, equipment, materials, housing and overhead. The salary schemes of hospitals and other healthcare suppliers will be used to estimate costs per hour for each healthcare professional. Taxes, social securities and vacations will be included.

Data on effects (reduction of HAI), costs (time costs of extra HH and material and development costs) and savings (reduced healthcare use of patients without HAI vs. comparable patients with HAI) will all be collected in this study. Data on treatment (hospitalisation) and follow-up consultations will be collected retrospectively from (electronic) patient charts and hospital administrations in a case-control study (60 cases, 60 controls). From each of the 4 strata (university teaching, non-academic teaching, large general, small general) 1 hospital will be selected for the case control study, and from this hospital 15 cases will be selected by the local ICP. Fifteen controls will be matched by characteristics such as age, sex and diagnosis on admittance. Since cost data per patient (but not per day care) are typically highly skewed, nonparametric bootstrap techniques will be used for calculating the differences in distributions of the direct medical costs. The data will be extracted from the patient files by a researcher using an anonymous data-collection form. Information will be collected on, among others, length of hospital stay, length of ICU stay, number of days on artificial ventilation, number of intravasal or urinary catheters placed and on antibiotic use.

To measure the economic impact of improved hand hygiene cost-effectiveness will be assessed by calculating the incremental cost-effectiveness ratio, defined here as the costs for the intervention (minus savings) divided by the difference in prevalence of HAI between the intervention and control group. Costs and effects will both be discounted with a 3% ratio. A sensitivity analysis will be performed to demonstrate the sensitivity of the results to changes in improved compliance under influence of process indicators (barriers and facilitators). Prognostic modelling will be used for a limited set of predictors of outcome (e.g. attendance of training sessions, alcohol hand rub availability, and frequency of feedback sessions by ICP).

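### The costing study compares whole admissions and names only admission characteristics for matching, so days before infection count as a cost of infection and savings per prevented HAI are biased upward

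*Protocol article*

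**What the plan says.** All of this stands in the Economic Evaluation section of the protocol article.

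- **Cost measure.** For the savings, "total intramural medical costs of comparable patients with HAI will be calculated".
- **Contrast.** The savings are defined as "savings (reduced healthcare use of patients without HAI vs. comparable patients with HAI").
- **Sample.** One hospital is taken from each of four strata: "1 hospital will be selected for the case control study, and from this hospital 15 cases will be selected by the local ICP".
- **Matching.** "Fifteen controls will be matched by characteristics such as age, sex and diagnosis on admittance".
- **Data extracted.** The examples given include "length of hospital stay, length of ICU stay, number of days on artificial ventilation". The date of infection onset is not among them.
- **Analysis.** "nonparametric bootstrap techniques will be used for calculating the differences in distributions of the direct medical costs".
- **Use.** The incremental cost-effectiveness ratio (ICER) is "the costs for the intervention (minus savings) divided by the difference in prevalence of HAI" between the arms. The sensitivity analysis described varies compliance under the influence of process indicators. It does not vary the cost attributed to an HAI.

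**The concern.** An HAI can occur only in a patient who is still in hospital. Someone who stays long for any other reason has more days in which to become a case, so long stay is partly a cause of infection and not only its result. A comparison of whole admissions counts the days before onset as if the infection had produced them. The same holds for ventilator days and catheters that preceded onset.

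Matching on age, sex and admission diagnosis does not remove this, because the bias arises even among patients who are identical at admission. The bootstrap deals with skewed costs, not with unequal time at risk.

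The saving per HAI is subtracted in the ICER numerator, so an overstated saving makes the package look cheaper per HAI prevented than it is. Costs per prevented HAI are research question 4 in the Objectives. The compliance and HAI comparisons between arms are not affected.

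**Working it through.** **1. The plan's own figure.** 4 strata × 1 hospital × 15 = 60 cases, and likewise 60 controls. This reproduces the stated size. The article states no attributable stay or cost per HAI, so there is no such figure to check.

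**2. Illustrative model (assumptions, not from the article).** All patients are alike at admission. Stay follows a gamma distribution with mean *m* and shape *k*; a larger *k* means less dispersed stays, and *k* = 1 is exponential. Infection strikes at a constant daily hazard *h* and does **not** change the stay, so the true excess is 0. With *a* = 1 + *hm/k*:

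- mean stay of never-infected patients = *m/a*
- mean stay of infected patients = *m*(1 − *a*^−(*k*+1)) / (1 − *a*^−*k*)

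Worked case, *m* = 10, *h* = 0.02, *k* = 1: *a* = 1.2. Controls 10/1.2 = 8.3 days. Cases 10 × (1 − 1/1.44)/(1 − 1/1.2) = 10 × 0.3056/0.1667 = 18.3 days. Spurious excess 10.0 days.

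| *m* (days) | *h* per day | *k* | cases | controls | spurious excess |
|---|---|---|---|---|---|
| 10 | 0.02 | 1 | 18.3 | 8.3 | 10.0 |
| 10 | 0.02 | 2 | 14.3 | 9.1 | 5.2 |
| 10 | 0.02 | 4 | 12.2 | 9.5 | 2.7 |
| 10 | 0.02 | 8 | 11.1 | 9.8 | 1.4 |
| 8 | 0.0125 | 1 | 15.3 | 7.3 | 8.0 |
| 8 | 0.0125 | 2 | 11.7 | 7.6 | 4.1 |
| 8 | 0.0125 | 4 | 9.9 | 7.8 | 2.1 |
| 8 | 0.0125 | 8 | 8.9 | 7.9 | 1.0 |

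**3. Allowing for the planned matching.** Let stay also vary between diagnostic strata (overall mean 10 days, coefficient of variation about 1, *h* = 0.02, no true effect) and match perfectly on stratum. In simulation the spurious excess falls from 8.8 to 4.2 days (within-stratum shape 4) and from 8.7 to 2.4 days (shape 8). Matching on diagnosis shrinks the bias but does not remove it.

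**4. If infection does prolong stay.** Simulation with constant hazards, mean uninfected stay 8 days, 10% infected, and infection multiplying the discharge hazard by the factor shown. The true excess is 8/factor − 8.

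| factor | true excess | whole-admission comparison | ratio |
|---|---|---|---|
| 1.0 | 0 | 8.0 | – |
| 0.8 | 2.0 | 10.2 | about 5 |
| 0.6 | 5.3 | 13.3 | 2.5 |

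Constant hazards mean *k* = 1, the most dispersed case in step 2, so these ratios are at the high end.

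**5. Does matching on time remove it?** Take as controls patients still admitted and uninfected on the case's onset day, and count stay from that day for both. Under no true effect, both have the same distribution of remaining stay, so the expected excess is 0. Under a true effect, about 10% of such controls become infected later, so the estimate is slightly diluted: 2.0 × 0.9 = 1.8 and 5.33 × 0.9 = 4.8 days for the last two rows of step 4. If controls must instead remain uninfected to discharge, a little upward bias stays: 0.8, 2.9 and 6.1 days for the three rows. Either choice is far closer to the truth than 8.0, 10.2 and 13.3.

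**The case against.** The strongest reply is that the article does not exclude matching on time. The matching variables are given as examples, the extracted items are introduced as part of a longer list, and a journal article condenses a fuller protocol that may hold the complete matching rule, the onset date and the costing window. This stands in part. The accurate statement is that time to infection is not *named*, not that it is ruled out. But the cost measure is stated as the total for the admission, and that choice conflicts with costing from onset.

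A second reply is that an excess of 8 to 10 days comes from exponential stays with no matching. That also stands. With less dispersed stays or matching on diagnosis, the figure is about 1 to 5 days. The direction was upward in every scenario.

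Two stronger readings are tempting and are not supported:

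- **Severe cases.** A reader might infer that selection by the local infection control practitioner favours memorable, severe infections. The text gives no selection rule, and consecutive selection from a surveillance list fits it equally well.
- **Long infections.** A reader might infer that cases come from the point-prevalence surveys, which would over-sample long infections and enlarge the bias. Nothing in the article says where the cases come from.

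Nor can agreement between a modelled prevalence and the plan's pooled 16% (Sample size calculations) support a particular infection hazard. It would require every infection to last until discharge.

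**Conclusion.** The concern holds in a limited form. As described, the costing compares whole admissions, and every matching variable named is known at admission. Days before onset then count as a cost of infection, savings per prevented HAI are biased upward, and the ICER is too favourable. The sensitivity analysis described would not reveal this.

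The direction follows from the design. The size does not: the article gives no stay, onset or cost data. For assumed mean stays of 8 to 10 days and no true effect, the spurious excess is about 1 to 10 days, with the upper end belonging to exponential stays without matching. No effect on the ICER in money can be computed. Confidence is moderate, since the full protocol may name further matching variables. This should be corrected before chart extraction, but it does not touch the primary outcome.

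**What to change.** In the Economic Evaluation section:

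1. Add the date of HAI onset to the data-collection form.
2. Besides age, sex and admission diagnosis, require each control to be still admitted and uninfected on the case's onset day, counted from admission.
3. Count costs and resource use from that day for both members of the pair, in place of totals for the admission.
4. State whether controls who become infected later remain in the comparison, since this decides between slight dilution and slight residual upward bias.
5. Vary the attributable cost per HAI in the sensitivity analysis, alongside compliance.

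The 60 + 60 patients and the chart sources stay the same. The price is one more extracted item and somewhat harder matching. If the full protocol already contains these rules, the article's wording needs only to say so.

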## Objectives

This study aims to evaluate the cost-effectiveness of the *ACCOMPLISH *package and will test the effects of this implementation strategy on HH compliance and prevalence of HAI. Furthermore, an economic evaluation will investigate the cost-effectiveness of this strategy from a healthcare perspective.

Research questions:

1. What is the effect of the multicomponent implementation strategy *ACCOMPLISH *on HH compliance rates?

2. Which process indicators contribute most substantially to observed changes in HH compliance?

3. What is the effect of the multicomponent implementation strategy *ACCOMPLISH *on the prevalence of HAI?

4. What is the balance between costs and health effects (costs per prevented HAI) of the *ACCOMPLISH *package?

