## Discussion

In this paper the ACCOMPLISH intervention study has been outlined. This study is the first RCT to investigate the effects of a HH intervention programme on the number of HAI, and the first to investigate the cost-effectiveness of such an intervention. Furthermore, this is one of the first interventions tailored to the different behavioural determinants of physicians and nurses.

Strengths of the study are number of participating centres, the cluster randomized controlled trial design and the length of follow-up (6, 12 and 18 months). Furthermore, the inclusion of not only a process measure (compliance) as outcome, but also the number of HAI and the cost-effectiveness study add to the strength of the study design. The limitations of the study are the use of prevalence rather than incidence data and the fact that that not all process evaluation instruments have been validated.

The results of the study will contribute to the body of evidence on influencing HH and shed light on the cost-effectiveness of such measures from a societal perspective. In addition, if the ACCOMPLISH package proves success in improving HH compliance and lowering the prevalence of HAI the package could be disseminated at national and international level.

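### The planned cost-effectiveness ratio is a cost per unit of HAI point prevalence reduced; without a conversion step it does not answer the trial's question of cost per prevented HAI

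*Protocol article*

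**What the plan says.** All references are to the Protocol article.

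- Objectives, research question 4: "What is the balance between costs and health effects (costs per prevented HAI").
- Economic Evaluation: the ratio is "defined here as the costs for the intervention (minus savings) divided by the difference in prevalence of HAI between the intervention and control group".
- Secondary outcome measure: "The prevalence rate is operationalized as the number of HAI per 100 patients". It is a survey measure: "Point-prevalence will be measured at T1, T2, T3 and T4 in all experimental and control units". Also: "At each data collection point two point-prevalence measurements will collected, and the data of the two measurements averaged to adjust for fluctuations".
- Economic Evaluation, savings: intramural costs of patients with HAI are set against those of comparable patients without, using 60 cases and 60 matched controls from four hospitals. Length of stay is among the items extracted.
- Economic Evaluation, sensitivity analysis: it varies improvement in compliance under the influence of process indicators. Duration of infection is not mentioned.
- Discussion: "The limitations of the study are the use of prevalence rather than incidence data", together with incomplete validation of the process instruments. The same section says the results will "shed light on the cost-effectiveness of such measures from a societal perspective", whereas Objectives and Economic Evaluation specify a healthcare perspective.

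**The concern.** The question is about infections that did not happen; the formula is about infections present on a survey day. The two differ by a factor that depends on duration. A patient with a long infection is more likely to be present at a survey, so a given fall in prevalence can stand for many short infections avoided or few long ones. The numerator accrues over a period, while the denominator is a cross-sectional figure.

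The savings term inherits the problem. The case-control study yields an extra cost per infected patient. To subtract it from programme costs, it must be multiplied by a number of infections prevented, and the text shown does not produce one.

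Cost-effectiveness is the study's stated aim and part of its claimed novelty. A figure reported as cost per infection prevented would feed the dissemination decision that the Discussion foresees, and could be compared with figures that really are per case.

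**Working it through.** **Scale of the planned effect.** Sample size calculations gives 8568 patients, a fall from 16% to 14% and 73% power at two-sided 0.05. With 1:1 allocation there are 8568/2 = 4284 per arm. The null standard error is √(2 × 0.15 × 0.85/4284) = 0.00772 and the alternative one is √((0.16 × 0.84 + 0.14 × 0.86)/4284) = 0.00771. Power = Φ((0.02 − 1.96 × 0.00772)/0.00771) = 73.6%, or 72.7% with continuity correction. The stated 73% reproduces, so the planned HAI effect is a 2-point difference in a prevalence proportion. (The calculation makes no allowance for clustering, which is a separate matter.) The article gives no figure for the ratio itself.

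**From prevalence to new infections.** In a steady state, with PD patient-days on the ward and mean infection duration D, prevalence P = (new infections × D)/PD. If D is the same in both arms, infections prevented are

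N = ΔP × PD / D.

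The stated formula contains ΔP but neither PD nor D.

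**Illustration.** The article gives no D and no ward census, so these values are assumptions. With ΔP = 0.02, each 1,000 patient-days carry 0.02 × 1,000 = 20 fewer infection-days:

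- D = 7 days: 20/7 = 2.86 infections prevented
- D = 14 days: 20/14 = 1.43
- D = 21 days: 20/21 = 0.95

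For an assumed 20 occupied beds over 18 months (20 × 365 × 1.5 = 10,950 patient-days), the counts are 0.02 × 10,950/D = 31.3, 15.6 and 10.4.

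**If duration differs between arms.** A fall from 16% to 14% needs no infection prevented at all if mean duration falls by 12.5% at fixed patient-days, since 0.16 × 0.875 = 0.14.

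**Effect on the ratio.** Let C be gross programme cost and s the saving per infection avoided. The net ratio per prevented infection is (C − sN)/N = C/N − s. The gross term C/N = C × D/(ΔP × PD) is proportional to D, so it triples from 7 to 21 days. The net ratio does not simply triple. Write c for gross cost per case at D = 7, so that it is 3c at D = 21:

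- s = 0.5c: the net ratio goes from 0.5c to 2.5c, a five-fold rise.
- s = 2c: it goes from −c (saving) to +c (net cost), a change of sign.

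**The case against.** **The cost base is not stated.** The article does not say whether costs are total, per ward or per patient. A reader might infer that total study costs are to be divided by 0.02; the text does not say so. Since the outcome is expressed as HAI per 100 patients, costs on the same base would give euros per HAI. This stands as far as it goes, but those HAI are prevalent, not new. Per 100 admissions, the difference in new infections is 2 × (mean stay of all patients)/(mean time from infection to discharge). With an assumed mean stay of 7 days, that is 2.0, 1.0 or 0.67 for 7, 14 or 21 days after infection. Only when the two times are equal do the measures agree.

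**The counts rest on assumptions.** This stands. A reader might take 8568/(32 wards × 4 time points × 2 surveys) = 33.47 as the daily ward census; 33.47 × 548 days × 0.02/7 would then give 52.4 infections prevented per ward, against 31.3 with 20 beds. The article does not say that 8568 counts all eight surveys, nor that a survey figure is a daily census. Such counts also apply the full effect from the first day, although nurse training runs over 3–4 months. The three-fold range is just 21/7, a ratio of two assumed durations.

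**The limitation is acknowledged.** The Discussion does name prevalence as a limitation, but it neither links this to the ratio nor renames the result.

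**A condensed article may leave detail to a fuller plan.** For the multiplication in the savings term this is fair, and that part carries less weight. It does not excuse the denominator, which is explicitly defined.

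**Conclusion.** The point holds for the ratio as defined: it is a cost per unit of HAI prevalence reduced, and it does not answer research question 4. The general limitation in the Discussion does not repair it.

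The size is indeterminate from the article. Gross cost per prevented infection is proportional to assumed duration; the net ratio can move by more or change sign. This rests on steady state, equal duration in both arms and a prevalence difference that persists over the patient-days it is applied to.

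A reader might infer that the trial can never yield a cost per prevented HAI, or that its effectiveness results are compromised. Neither follows. A stated conversion would supply the missing quantity, and the compliance and HAI prevalence comparisons do not use this ratio.

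Separately and minor, the societal perspective in the Discussion conflicts with the healthcare perspective elsewhere. No listed cost item depends on it, and it adds nothing to the main point.

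**What to change.** - Define infections prevented as a modelled quantity: (between-arm prevalence difference × patient-days on the intervention wards) / mean infection duration. Use the same number in the denominator and to scale the per-case savings.
- Take duration from the chart review, not from survey dates. Infections found at a survey are length-biased, and those still active have no end date. Say how the 60 cases are found, because cases drawn from survey lists would carry the same length bias.
- State the assumption of equal duration in both arms, and add duration to the sensitivity analysis.
- If patient-days or durations cannot be obtained, report cost per percentage point of HAI prevalence reduced and reword research question 4.
- Reconcile the perspective named in the Discussion with Objectives and Economic Evaluation.

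The cost is one formula, onset and resolution dates on the existing extraction form, ward patient-day counts and one more sensitivity range. The downside is an added modelling assumption, resting on charts from four hospitals. Design and outcome measurement stay as they are.
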